#### Enrolment and consent of physicians

At each site, we will recruit clinicians whose responsibilities include the care of paediatric diarrhea patients. Study staff will determine if the clinician is eligible and then provide detailed information of the study. Once the clinician exhibits understanding, written consent will be obtained. There will be two questionnaires administered: 1) before, and 2) after the study period. The post-study questionnaire will also include a brief focused interview. Only clinicians who have completed the entire study will be eligible for this questionnaire.

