### Outcome measures/variables:

The primary outcome is the proportion of children given antibiotic prescriptions, as assessed by hospital records. Secondary outcomes are the proportion of children with resolution of diarrheal symptoms at 10-days after enrollment, and clinician satisfaction towards use of the DEP, as assessed by pre- and post-study questionnaires

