## Description of the Research Project

**Hypothesis to be tested:** We hypothesize that Diarrheal Etiology Prediction (DEP) algorithm for calculating probability of viral etiology of diarrhea will safely reduce inappropriate antibiotic use among children <5 years old with acute diarrhea.

**Primary objective:** To examine the acceptability and impact of a Diarrheal Etiology Prediction (DEP) among physicians treating children with diarrhea.

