### Clinical setting:

The clinical approach will adhere to World Health Organization guidelines for the management of uncomplicated diarrhoeal disease in children with No, Some and Severe dehydration. These guidelines have previously been adapted to a digital format (e.g. Rehydration Calculator) and evaluated in a pilot and cluster randomized controlled trial (icddr,b/ IEDCR; Khan AI et al, submitted 2019 and Haque et al. PLoS NTD 2017); clinically relevant outcome measures in these studies were equivalent or improved with digital decision-support. The Rehydration Calculator version to be used in this study will include unchanged weights estimations and oral and intravenous (IV) fluid calculations; changes will include elimination of the antibiotic recommendations and replacement with the viral diarrhea probability. 15 physicians across 4 facilities will be enrolled.

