## a. Detailed Research Methods

### c.i. Study design.

This is a randomized crossover study, where clinicians will be randomized to periods where they will use a rehydration calculator application with or without the DEP algorithm. The crossover will include a washout period to reduce carryover effect. The study will be conducted over a 9-week period. We will use a random number generator to randomize clinicians to DEP (use of the etiology calculator) or control arm (use of a previously-tested rehydration calculator) within site for the first 4 weeks. After the first 4 weeks, there will be 1-week washout period without decision support, after which each clinician will cross-over to the other arm for the next 4 weeks.

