#### c.iii. Data collection

**Clinicians:** We will use a screening form (Appendix 3) and questionnaire (Pre- and post-Study) to collect quantitative (Appendix 4 & 5) data regarding clinician attitudes and experiences using the App and its role in diarrheal management. These questionnaires will be administered by study coordinators at 2 time points: 1) at the start of the study, and 2) at the end of the study. We will also use the App itself to collect data regarding physician usage.

**Children:** For each enrolled patient, study staff will collect:

- At enrolment, demographic and clinical variables
- At discharge, hospital outcome measures, including intravenous and oral fluids, and antibiotics, zinc administered
- At 10-days post-discharge, health outcomes including persistence of diarrheal and abdominal symptoms, returns to healthcare, and medication use since discharge, will be collected over a phone call.

**Instruments:** As mentioned, electronic tools that are compliant to the protections of PHI (Protected Health Information) will be used in this study. These include the Outbreak Responder software, which includes the DEP, and if needed, RedCap.

**Data Storage:** Data collected on Outbreak Responder software will be stored on a secure cloud-based server (server is physically based in Singapore; this is a HIPAA compliant server managed by Amazon Web Services).

Access to the server(s) will be restricted and the server management conforms to industry standard for health information.

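### The post-study questionnaire is closed to clinicians who do not complete the study, so satisfaction with the DEP may be biased, probably upward, if those who dislike the tool withdraw

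*Protocol*

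**What the plan says.** The primary objective (Description of the Research Project) is "To examine the acceptability and impact of a Diarrheal Etiology Prediction (DEP) among physicians treating children with diarrhea". Under Outcome measures/variables, the secondary outcomes include "clinician satisfaction towards use of the DEP, as assessed by pre- and post-study questionnaires". The primary outcome is antibiotic prescription.

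Section c.iii (Data collection) sets two time points for the clinician questionnaires: "1) at the start of the study, and 2) at the end of the study". No questionnaire is planned at the crossover or at withdrawal. Enrolment and consent of physicians adds a brief interview to the second questionnaire and then restricts access to it: "Only clinicians who have completed the entire study will be eligible for this questionnaire". The Staff Training paragraph, which precedes that section, describes doctors answering before and after the study and sets no such condition.

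On scale and schedule, Clinical setting states that "15 physicians across 4 facilities will be enrolled". Section c.i (Study design) states "The study will be conducted over a 9-week period" and says of what follows the first 4-week period that "there will be 1-week washout period without decision support, after which each clinician will cross-over to the other arm for the next 4 weeks". Data Analysis plans descriptive tables for the survey.

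**The concern.** The pre-study questionnaire precedes any study use of the DEP, so only the post-study questionnaire and interview can capture a clinician's opinion after using it. The restriction removes clinicians who used the DEP and then left, and some of them may have left because of the tool. It is also stricter than the outcome needs. A clinician randomised to the DEP first could use it for all 4 weeks, leave during the washout or the control period, and still be barred.

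This is a rule about what data are collected, so a statistical analysis plan cannot repair it: a questionnaire never given cannot be imputed with any confidence in a group of 15. It also means that the pre-study answers would cover everyone enrolled while the post-study answers would cover completers only, so the two sets of tables could describe different people.

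A second, smaller matter is timing. Everyone answers at the end of the study, but the interval since last using the DEP depends on the randomised sequence.

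**Working it through.** **Inputs from the protocol.** 15 clinicians (Clinical setting); a first period of 4 weeks, a washout of 1 week and a second period of 4 weeks, 9 weeks in all (section c.i); post-study questionnaire at study end only (section c.iii), for completers only (Enrolment and consent of physicians).

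**Assumed input.** The number of clinicians lost, d. The protocol gives no clinician dropout rate, so d = 0 to 4 is shown.

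**Step 1. The plan's own figure.** 4 + 1 + 4 = 9 weeks, which agrees with the stated study length.

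**Step 2. Weight of one clinician.** 1/15 = 6.7 percentage points.

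**Step 3. Bounds.** With d lost there are 15 − d completers. If s of them are satisfied, the reported value is s/(15 − d). Over all 15 clinicians the value lies between s/15 (no leaver satisfied) and (s + d)/15 (every leaver satisfied).

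If every completer is satisfied, s = 15 − d and the report is 100%:

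| Lost (assumed) | Reported | Lowest value over all 15 |
|---|---|---|
| 0 | 15/15 = 100% | 15/15 = 100% |
| 1 | 14/14 = 100% | 14/15 = 93.3% |
| 2 | 13/13 = 100% | 13/15 = 86.7% |
| 3 | 12/12 = 100% | 12/15 = 80.0% |
| 4 | 11/11 = 100% | 11/15 = 73.3% |

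**Step 4. Direction.** The bias need not be upward. With 3 lost and 10 of 12 completers satisfied, the report is 10/12 = 83.3%. The value over all 15 then lies between 10/15 = 66.7% and 13/15 = 86.7%, an interval that contains values above the report. The bias is upward only if leavers are less satisfied than completers. That is the more plausible case, but the protocol does not establish it.

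**Step 5. Time since last DEP use at study end.** DEP-first clinicians stop using it at the end of week 4, so 9 − 4 = 5 weeks (1 washout + 4 control). Control-first clinicians stop at the end of week 9, so 9 − 9 = 0 weeks. If the questionnaire is given somewhat after week 9, both intervals lengthen equally and the 5-week difference remains. Unlike the selection effect, this difference does not depend on dropout.

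**The case against.** The strongest reply is that the harm is conditional and the outcome is minor. The protocol gives no dropout rate and no reasons for leaving. It excludes clinicians who already plan to leave the site, and the study lasts only 9 weeks, so losses may be few or none. Satisfaction is a secondary outcome summarised in tables, no test or decision rests on it, and the antibiotic endpoint is untouched. The app also logs usage without a completers-only limit, so disuse can be seen even in those who leave. All of this stands and limits the weight of the point. Usage logs do not replace the questionnaire, however, because they show whether the tool was opened, not what the clinician thought of it or why it was abandoned.

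A reader might infer three stronger things that the documents do not support:

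- **That acceptability is biased upward.** This needs both dropout and lower satisfaction among those who drop out, and neither is documented.
- **That clinicians who stop using the app are barred.** The rule concerns completing the study and does not mention app use. Someone who stops opening the app but stays enrolled is not clearly excluded, and completion is not defined.
- **That the questionnaire must move to the end of each clinician's DEP period.** That would equalise recall, but DEP-first clinicians would then answer before using the control app, while control-first clinicians would answer after using both. It would also place an interview about the DEP just before the washout and control period of one sequence only, which could add to the carryover that the washout is meant to reduce. It is a trade-off, and the direction of any recall effect is unknown.

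**Conclusion.** The point holds as a conditional risk to a secondary outcome. The completers-only rule is explicit, is narrower than the Staff Training paragraph, and discards post-use opinions that could be had at almost no cost. If clinicians who dislike the DEP withdraw, satisfaction will probably be overstated. In the extreme case where all completers are satisfied and no leaver is, the overstatement is 6.7 points for each clinician lost, reaching 100 − 73.3 = 26.7 points with 4 lost. These sizes rest on assumed losses, and with full completion there is no selection bias.

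The 5-week versus 0-week difference follows directly from the schedule. It affects how answers from the two sequences compare, in an unknown direction, and calls for showing results by sequence rather than for a change of timing. The primary antibiotic comparison is not affected.

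**What to change.** 1. Delete the completers-only sentence from Enrolment and consent of physicians, which also brings that section into line with the Staff Training paragraph.
2. Give the same questionnaire and interview to every clinician who was issued the DEP: at withdrawal for those who leave early, and at study end for everyone else. A control-first clinician who leaves before being issued the DEP has no experience of it to report and is simply counted under item 3.
3. Report how many enrolled clinicians did not respond.
4. Tabulate satisfaction by randomised sequence. With 15 clinicians there would be about 7 or 8 per sequence if the split is near equal (15/2 = 7.5), so this is descriptive only.

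The cost is one exit interview for each clinician who withdraws. The instrument, the coordinator and the end-of-study timing for completers stay as they are.

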#### Enrolment and consent of patients

Study staff will be situated in the intake areas and will identify children 2–59 months with diarrhoeal illness. Study staff will select consecutive subjects between 8am and 2pm on weekdays for enrolment on arrival to the Hospital. Potential participants' information (age and time of intake, etc) will be recorded in a screening log. Study staff and nurses will inform parents or primary caretakers (PPC) of patients who meet the inclusion/exclusion criteria about the study. If PPC is interested in the study, study staff will determine if the child is eligible and then provide more detailed information to the PPC's of eligible subjects. Detailed information will be provided in French and will include goals, risks, and benefits of the study. Once the PPC exhibits understanding, written consent will be obtained in the local language prior to enrolling the subject in the study. Illiterate PPC's will give consent by marking the consent form with their thumbprint or signature after a study staff member reads the consent form in French. Children without a PPC present will be excluded from the study. The last signature on the consent will be from the enrolling staff member.

#### c.iii. Data collection

**Clinicians:** We will use a screening form (Appendix 3) and questionnaire (Pre- and post-Study) to collect quantitative (Appendix 4 & 5) data regarding clinician attitudes and experiences using the App and its role in diarrheal management. These questionnaires will be administered by study coordinators at 2 time points: 1) at the start of the study, and 2) at the end of the study. We will also use the App itself to collect data regarding physician usage.

**Children:** For each enrolled patient, study staff will collect:

- At enrolment, demographic and clinical variables
- At discharge, hospital outcome measures, including intravenous and oral fluids, and antibiotics, zinc administered
- At 10-days post-discharge, health outcomes including persistence of diarrheal and abdominal symptoms, returns to healthcare, and medication use since discharge, will be collected over a phone call.

**Instruments:** As mentioned, electronic tools that are compliant to the protections of PHI (Protected Health Information) will be used in this study. These include the Outbreak Responder software, which includes the DEP, and if needed, RedCap.

**Data Storage:** Data collected on Outbreak Responder software will be stored on a secure cloud-based server (server is physically based in Singapore; this is a HIPAA compliant server managed by Amazon Web Services).

Access to the server(s) will be restricted and the server management conforms to industry standard for health information.

### **Sample Size Calculation and Outcome (Primary and Secondary) Variable(s)**

For estimated 90% of children receiving antibiotics in control arm (per mHDM study), and estimated 80% of children receiving antibiotics in DEP arm, along with a within- and between- period correlations for each physician of 0.15, a sample size of 360 children (**15 clinicians**, with 2 cross-over periods and 12 patients during each period) will achieve a power above 95% to detect a 2-sided significance of 0.05. If enrolment is reached prior to the pre-determined study period, enrolment will be continued until the end of the study period; this is important given that aspects of the study outcomes are dependent on weeks of use.

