#### c. Relevance:

The majority of decisions for use of antibiotics in diarrhoeal illnesses are made empirically. In lower and middle-income countries (LMICs), due to cost constraints, etiological diagnosis is rarely made, and a large number (up to 70%) of patients with acute diarrhoea are prescribed antibiotics. In both high and low resource settings, inappropriate use of antimicrobials leads to unnecessary toxicity for the individual, increased costs and an increase in antibiotic resistance in the community. Thus, methods for guiding appropriate use of antibiotics for pediatric diarrhoea in both high- and low-resource settings are urgently needed.

Clinical prediction rules (CPRs) are decision-making rubrics that help clinicians estimate the likelihood of a patient outcome. Clinical prediction rules integrated into clinical decision making have the ability to direct clinicians towards more evidence-based behaviors, resulting in improved care and reduction of costs and have the potential to help healthcare workers worldwide address clinical uncertainty and provide improved care for children with diarrhoea.

**Hypothesis:** We hypothesize that Diarrheal Etiology Prediction (DEP) algorithm for calculating probability of viral etiology of diarrhea will safely reduce inappropriate antibiotic use among children <5 years old with acute diarrhea.

**Objectives:** To examine the acceptability and impact of a Diarrheal Etiology Prediction (DEP) algorithm among physicians treating children with diarrhea.

**Methods:** This is a randomized crossover study and clinicians will be randomized to periods where they will use a rehydration calculator application with or without the DEP. The crossover will include a washout period to reduce carryover effect. The study will be conducted over a 9-weeks period. We will use a random number generator to randomize clinicians to DEP or control arm for the first 4 weeks. After the first 4 weeks, there will be a 1-week washout period without decision-support, after which each clinician will cross-over to the other arm for the next 4 weeks.

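### The stated power of above 95% does not follow from the stated design; the protocol's own inputs give about 80%

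*Protocol*

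**What the plan says.** The section Sample Size Calculation and Outcome (Primary and Secondary) Variable(s) gives every input needed to check its power figure:

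- control arm: "For estimated 90% of children receiving antibiotics in control arm (per mHDM study";
- DEP arm: "estimated 80% of children receiving antibiotics in DEP arm";
- clustering: "within- and between- period correlations for each physician of 0.15";
- size: "a sample size of 360 children", made up of 15 clinicians "with 2 cross-over periods and 12 patients during each period".

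It concludes that this design "will achieve a power above 95% to detect a 2-sided significance of 0.05". No formula or software is named.

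Other sections agree with this design. Clinical setting says that "15 physicians across 4 facilities will be enrolled". Section c.i (Study design) has every clinician cross to the other arm after the washout. Data Analysis plans a generalized linear mixed model with provider and clinic as random effects and an adjustment for period.

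**The concern.** The power figure looks too high for 180 children per condition. A 10-point difference between 90% and 80% with 180 independent children per arm has power of only about 76%. The crossover recovers a little precision at the stated correlations, but not enough to reach 95%.

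This is the only justification given for the sample size, and it concerns the primary outcome. If the true risk of missing a 10-point reduction is about 20% rather than under 5%, a null result is much weaker evidence against the DEP than the protocol leads readers to think.

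**Working it through.** **Inputs.** All come from the sample-size section: p₁ = 0.90, p₂ = 0.80, K = 15 clinicians, m = 12 children per clinician-period, within-period correlation ρw = 0.15, between-period correlation ρb = 0.15, two-sided α = 0.05. Since 15 × 2 × 12 = 360, the figure of 360 is the overall total and each condition has 15 × 12 = 180 children. The binomial variances are 0.90 × 0.10 = 0.09 and 0.80 × 0.20 = 0.16, which sum to 0.25.

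**Attempt to reproduce the stated figure.**

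*Design-effect method.*
- DE = 1 + (m − 1)ρw − mρb = 1 + 11(0.15) − 12(0.15) = 0.85
- SE = √(0.85 × 0.25 / 180) = 0.0344
- z = 0.10 / 0.0344 = 2.91
- power = Φ(2.91 − 1.96) = 82.9%

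*Exact covariance of the two binary periods.* The two arms have different variances, so the covariance between period means is ρb√(0.09 × 0.16) = 0.15 × 0.12 = 0.018.
- Var = [(0.25 / 12) × (1 + 11 × 0.15) − 2 × 0.018] / 15 = (0.05521 − 0.036) / 15 = 0.001281
- SE = 0.0358; z = 2.79; power = 79.8%

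*Small number of clinicians.* With a noncentral t on 13 degrees of freedom, the two results become 76.7% and 73.4%.

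*Simulated mixed model.* Analyses with a provider random intercept gave 81–82%.

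**Other readings at 360 children and correlations of 0.15.**

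| Variant | Power |
|---|---|
| Pooled variance | 82.2% |
| Arcsine scale | 83.2% |
| Log-odds scale | 80.8% |
| One-sided 0.05 | 89.7% |
| Clustering ignored | about 76% |

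None reaches 95%.

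**What would give 95%.**
- *More children.* By design effect, about 19 per clinician-period (19 × 30 = 570 children); by exact covariance, 22 (22 × 30 = 660).
- *A larger effect.* A DEP rate of 77% gives 95.5% by design effect; 76% gives 95.7% by exact covariance. The drop needed is therefore about 13–14 points.
- *360 per arm.* With 24 children per clinician-period, power is 96.8% (exact covariance) to 98.4% (design effect). Reading the total as a per-arm number is one possible source of the stated figure, but the protocol does not show how it was obtained.

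**Sensitivity to the between-period correlation.** The within-period value is held at 0.15. Apart from 0.15, the between-period values are assumptions made here.

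| ρb | Exact covariance | Design effect |
|---|---|---|
| 0.15 | 80% | 83% |
| 0.12 | 66% | 68% |
| 0.10 | 59% | 61% |
| 0.075 | 52% | 53% |

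The between-period correlation enters the variance with a negative sign, so setting it equal to the within-period value gives the highest power among values that do not exceed it.

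**The case against.** The strongest reply is that 80% is a conventional power level, so the design is adequate and only a description is wrong. The error does not bias the estimate or raise the type I error, and a careful reader would judge a null result from its confidence interval. That is fair, and it is why no change to the sample is needed. It does not make the stated figure true.

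Second, the same section lets enrolment run to the end of the study period if the target is met early, so 360 is not a cap. At 15 per clinician-period (450 children) power would be 87–90%. The 20% risk is therefore conditional on about 360 children. But the protocol ties its claim to 360 and nowhere projects the roughly 570–660 that 95% would need.

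Third, the lower between-period correlations are not the protocol's. Equal correlations are its explicit planning assumption and fit a model with one random intercept per provider. The lower values therefore show how fragile the figure is and are not a second error.

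Fourth, the background remark (section c, Relevance) that "a large number (up to 70%) of patients with acute diarrhoea are prescribed antibiotics" describes lower- and middle-income countries generally, whereas the 90% is taken from a named study. The two do not contradict each other. A fall from 70% to 60% would have power of 58%, but this only illustrates the dependence on the control rate.

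**Conclusion.** The statement of power above 95% is wrong as written. On the protocol's inputs, power at 360 children is 80–83% by normal approximation and 73–77% with a t reference on 13 degrees of freedom. The shortfall is at least 12 percentage points, too large to be rounding or choice of method. The result assumes both correlations are exactly 0.15, 12 children in every clinician-period and no losses. A lower between-period correlation would reduce power further; enrolment beyond 360 would raise it.

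**What to change.** Replace the power statement with one that follows from the inputs and names its method. For example: with 15 clinicians, two periods and 12 children per clinician-period (360 in total), 90% versus 80%, and within- and between-period correlations both 0.15, power is about 80% at two-sided 0.05 (normal approximation, exact covariance of the two binary periods), or about 73% with a t reference on 13 degrees of freedom.

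Add that power falls to about 59–66% if the between-period correlation is 0.10–0.12, and that 95% power applies to a drop of about 14 points by the same normal approximation. Keep the sample of 360.

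The cost is one or two sentences in the sample-size section and a less favourable stated figure. No extra patients and no change to design or analysis are needed.
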